### Intervention arm: AI-enabled stethoscope

This study will investigate the impact of an AI-enabled stethoscope (henceforth referred to as AI stethoscope) with integrated sensor technology—electrodes and a microphone—for recording digital single-lead ECG and PCG (Eko DUO, Eko Health Inc, California, USA). The AI stethoscope works as a conventional stethoscope with diaphragm and detachable tubing that enables conventional auscultation, with other features including noise filtration and cancellation. The device connects to an app on the user’s smartphone (Eko: Digital Stethoscope+ECG, Eko Health, USA) using Bluetooth connectivity for waveform visualisation. Connectivity via cellular/Wi-Fi allows access to cloud-based AI algorithms for analysis of waveforms (no data is stored in the AI stethoscope or user’s smartphone).

The AI stethoscope and associated AI algorithms are regulated by the UK Medicines and Healthcare Products Regulatory Agency (MHRA) and are UKCA-marked as Class IIa medical devices, respectively. This means that they are authorised for use in clinical care in the UK, in accordance with their regulated intended purpose.

The AI stethoscope is provided as a replacement stethoscope for routine patient clinical examination. Use of the AI stethoscope will be at the discretion of the responsible clinician, with no patient-level inclusion or exclusion criteria. The additional functionality in the form of AI algorithms for HFrEF, AF and VHD detection will be used within its regulated intended purpose. As established by previous studies,^26^ the optimum unit of examination to derive AI insights entails placing the device–‘listening’–over the pulmonary position (upper left sternal border) and taking a 15-s recording.

In an NHS first, the clinical guidelines for actioning AI outputs have been agreed by the Cardiovascular Executive Groups of the NHS North West London Integrated Care System and Betsi Cadwaladr University Health Board (online supplemental figure 1). Patients will be examined with the AI stethoscope in accordance with these guidelines, and/or where stethoscope examination is deemed clinically appropriate by the primary care clinician. Patients will provide verbal consent for examination with the AI stethoscope as per any physical examination performed by healthcare professionals for direct care purposes, in accordance with UK law and General Medical Council guidelines.^41^

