### Data sources

In the NWL ICS, patient-level complete primary and secondary care clinical and cost data is pseudonymised and pooled within Discover-NOW, a UK Trusted Research Environment.^37^ AI stethoscope usage statistics and AI predictions will be integrated into the Discover-NOW and tagged to appropriate patient records. The study team will access this real-world data platform to measure population-level clinical and health economic outcomes, in addition to patient-level sensitivity analyses for NWL ICS.

At BCUH, only the direct care team will access medical records and record population-level outcomes as part of a service evaluation (coprimary endpoints), using epidemiological methods only.

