### Statistical analysis

Baseline patient-level data in NWL will be extracted at the index date, defined as the date of first examination using the AI stethoscope at each primary care practice. Data will be summarised as mean (SD) or median (IQR) for skewed data. Comparisons between groups will be undertaken on an intention-to-treat basis, using two-sample t tests for continuous variables, and χ^2^ tests for binary and categorical variables. For each outcome, we will perform generalised mixed-effect logistic regression to compare the study arms, with the GP practice as a random effect.

Subgroup analyses for patient-level outcomes will be performed, stratified by age, sex, ethnicity and geography, patient comorbidities and GP practice characteristics (mean age of clinicians, size of clinical team, number of registered patients).

Patient-level sensitivity analyses will be performed for patients with abnormal AI-stethoscope predictions for HF to identify direct associations between AI stethoscope predictions and specific diagnostic codes for HF, AF and VHD.

We will measure relationships between items in the clinician questionnaire, utilisation rates of the AI stethoscope, compliance with recommendations and the primary endpoints. These analyses will identify domains that are most strongly related to utilisation and compliance, which will help improve the technology, and guide future implementation and clinical pathways.

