This study is both decentralised and principally uses ‘real-world’ data; there is no lead/central study site or logistics/travel outside each GP practice. Each will contribute data equally, but without the need to complete any study-specific (cumbersome) data collection instruments. Instead, our use of Discover-NOW enables outcomes measurement with routinely recorded (real world) data. The platform’s offer of comprehensive linked (primary and secondary care) clinical and cost data affords patient-level sensitivity analyses. This will allow robust measurement of associations between diagnostic outcomes and use of the AI stethoscope. Separate to such novel elements of this study, TRICORDER has set several other important precedents for translational AI research, including approval of the first regional NHS clinical guideline for the use of a primary care focused AI technology, and sector-wide data governance approval covering use of an AI technology across hundreds of disparate primary care sites.

This research protocol is best interpreted in the context of its limitations. The pragmatic design, which aims to have a minimal impact on GP workflows, may in some cases limit sustained use of the technology by not setting any expectations or requirement for use—though this may somewhat mitigate any Hawthorne effect.^49^ This study is the first to accompany a novel AI technology with an NHS sector-approved clinical guideline for use, but variable adherence may limit the impact attributable to the technology. This will be addressed systematically, taking an implementation science approach to maximise uptake of the intervention. Finally, the examination of real-world data is universally limited by the inconsistency and variable fidelity of medical coding in capturing specific variables of interest. For example, for HF, this is rarely coded with a granularity that describes preserved, moderately reduced or reduced ejection fraction. However, the otherwise comprehensive data flows associated with this study will allow holistic scrutiny of a broad selection of outcomes that need to be understood to underpin any recommendations for system-wide uptake. Ultimately, this will serve to provide a realistic estimate of the potential clinical and health economic impact of the AI stethoscope technology in NHS primary care.

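### The patient-level sensitivity analysis is limited to patients with an abnormal HF prediction, so the HF flag has no contrast and AF and murmur results are studied only in an HF-selected subgroup

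*Protocol article*

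**What the plan says.** The protocol article, under Statistical analysis, gives the analysis set and the aim in one sentence: "Patient-level sensitivity analyses will be performed for patients with abnormal AI-stethoscope predictions for HF to identify direct associations between AI stethoscope predictions". The outcomes it lists are codes for all three conditions: HF, AF and VHD. It names no reference group, whether AI-normal, unexamined or control-arm patients.

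Three other places bear on it:

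- **Intervention arm: AI-enabled stethoscope.** The device runs separate algorithms for three conditions: "The additional functionality in the form of AI algorithms for HFrEF, AF and VHD detection will be used within its regulated intended purpose".
- **Data sources.** Device output is linked to records without a stated limit to abnormal results: "AI stethoscope usage statistics and AI predictions will be integrated into the Discover-NOW and tagged to appropriate patient records". Patient-level work is confined to North West London: "in addition to patient-level sensitivity analyses for NWL ICS".
- **Discussion.** Of the linked platform and the patient-level sensitivity analyses in general, the article says: "This will allow robust measurement of associations between diagnostic outcomes and use of the AI stethoscope".

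**The concern.** An association between a prediction and a diagnosis needs patients with and without the prediction. The sentence selects patients on an abnormal HF prediction and then asks how predictions relate to three diagnoses. For the HF flag this removes the contrast. For the other two algorithms it keeps a contrast but applies a selection rule that has nothing to do with the AF or murmur result, although AF and VHD codes are among the outcomes.

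At stake is the article's one stated patient-level analysis that links what the device reported to what was later coded. Clinicians choose whom to examine, so examined patients may have a higher rate of new diagnoses than the practice list whatever the device shows. A proportion taken from flagged patients alone cannot be set against that background.

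**Working it through.** The article gives no sample size, effect size or accuracy figure for this analysis, so there is no stated figure to reproduce. The check is whether each association can be estimated at all.

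**1. HF flag in the planned set.** With F = 1 for an abnormal HF prediction, every patient in the set has F = 1. The two-by-two table of F against any code has an empty F = 0 row. The odds ratio (a × d)/(b × c) has c = d = 0 and is undefined. Equivalently, a logistic model with an intercept and F has a design matrix of rank 1, not 2. What remains is a/(a + b), the proportion coded.

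**2. What that proportion cannot show (assumed rates).** Let 10% of flagged patients receive an HF code.

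- If 1% of AI-normal patients are coded, the risk ratio is 10%/1% = 10.
- If 10% of AI-normal patients are coded, it is 10%/10% = 1.

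The planned set returns 10% in both cases.

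**3. HF flag once AI-normal patients are included.** None of these inputs is in the article; all are assumptions: HF prevalence p of 2% or 5% among examined patients, sensitivity = specificity = s of 0.7, 0.8 or 0.9, and a code that matches true disease.

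- Odds ratio = [s/(1 − s)]². This gives (0.7/0.3)² = 5.4, (0.8/0.2)² = 16 and (0.9/0.1)² = 81.
- Proportion coded among flagged = ps/[ps + (1 − p)(1 − s)]. The lowest value is 0.014/(0.014 + 0.294) = 4.5%, at p = 2% and s = 0.7. The highest is 0.045/(0.045 + 0.095) = 32%, at p = 5% and s = 0.9.

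Simulation under the same assumptions agrees: odds ratios of about 5 to 85 in all examined patients, undefined in the HF-abnormal set, and a proportion coded of about 4% to 32%.

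**4. AF result in the planned set.** The AF result still varies, and the design matrix has rank 2 of 2. Further assumptions are AF prevalence of 30% with HF, 3% or 6% without HF (paired with HF prevalence of 2% and 5%), and independent test errors. The simulated odds ratio of AF result with AF code is then about 5.5 to 83 in the HF-abnormal set and 5.5 to 82 in all patients. The pair can be estimated. Similar values in the two sets follow from assuming independent errors, which recordings from the same 15-second examination need not satisfy. The same reasoning applies to the murmur result and VHD code.

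**5. Who is left out.** Worked for p = 2%, s = 0.8 and AF prevalence of 3% without HF:

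- Abnormal AF result with HF: 0.3 × 0.8 + 0.7 × 0.2 = 0.380. Without HF: 0.03 × 0.8 + 0.97 × 0.2 = 0.218.
- All with an abnormal AF result: 0.02 × 0.380 + 0.98 × 0.218 = 0.2212.
- AF and HF results both abnormal: 0.02 × 0.8 × 0.380 + 0.98 × 0.2 × 0.218 = 0.0488.
- Left out: 1 − 0.0488/0.2212 = 78%.

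| HF prevalence (AF without HF) | s = 0.7 | s = 0.8 | s = 0.9 |
|---|---|---|---|
| 2% (3%) | 69% | 78% | 86% |
| 5% (6%) | 67% | 75% | 81% |

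These shares show scale under the assumptions; they are not estimates for this trial.

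**The case against.** **A condensed article.** The sentence does not say that only flagged patients are used, and a full protocol or analysis plan, not shown here, may name a reference group. That is fair as far as the missing comparator goes. But the article does state a population, and followed as written that population does not serve the aim given in the same sentence. This is more than omitted detail.

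**No association at all.** A reader might infer that the analysis can estimate nothing but a proportion. The documents do not support that. The sentence speaks of AI predictions without limiting them to HF, and there are three algorithms. AF and murmur results vary among HF-flagged patients, so those pairs can be estimated in that subgroup. A continuous HF score, if one were used, would also give a gradient; the article does not mention one.

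**The Discussion's claim.** A reader might also infer that the Discussion's promise of robust measurement rests on this sentence alone. It does not. That statement is about use of the device and credits linked data and patient-level sensitivity analyses generally. The Statistical analysis section separately relates utilisation and compliance to the primary endpoints.

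**Counting the patients lost.** It is tempting to turn the Sample size section's 60 patients per practice-year into a number of discarded patients. That does not work. The 60 are routine stethoscope examinations, while AI use is discretionary, and patient-level analysis excludes North Wales.

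**Bias in the alternative.** An abnormal-versus-normal comparison of codes is affected by differential work-up, because AI-normal patients are less likely to be sent for confirmatory tests. The proportion of flagged patients later coded is a legitimate and easily read result. Both points stand, and the fix has to carry them.

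**Conclusion.** The concern holds in a limited form. As written, the analysis cannot estimate the association of a binary HF flag with HF, AF or VHD codes; it gives only the proportion of flagged patients later coded. AF and murmur results can be related to their codes, but only in a subgroup selected on the HF result. Under the assumed inputs, that subgroup omits about two thirds to 86% of patients with an abnormal AF result.

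The HF conclusion rests on two readings: that the sentence defines the whole analysis set, and that the HF output is used as a binary flag. It does not depend on the assumed accuracies or prevalences, which serve only to show scale.

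The consequence is confined to a secondary explanatory analysis. The randomised coprimary comparison and the between-arm comparisons of AF and VHD codes are untouched.

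**What to change.** Redefine the set as all North West London patients with an interpretable AI-stethoscope recording. Relate HF code to HF result, AF code to AF result and VHD code to murmur result, each abnormal versus normal, in the mixed-effects logistic model already planned, with practice as a random effect.

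Report separately, for each algorithm, the proportion of abnormal results followed by the matching code. State as a limitation that AI-normal patients are less likely to receive confirmatory testing, so the association partly reflects differential work-up.

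If the abnormal-only set is kept, restate the aim as the proportion of abnormal HF predictions followed by a code, and drop the wording about associations.

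The cost is a sentence or two of analysis text. Since the article describes linkage of AI predictions with no limit to abnormal results, no new data collection appears to be needed.

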### Interim analysis

An interim analysis will be performed 6 months after the first site has been randomised. The interim analysis will report the following selected outcomes and will be reviewed by the Trial Steering Committee, who will remain blinded to the treatment allocation of each group until the study end:

Coprimary endpoints:

Difference in the incidence of coded HF between groups;Difference in the ratio of coded HF incidence via hospital admission-based versus community-based diagnostic pathways between groups

Secondary endpoints

Healthcare diagnostics utilisationPrimary care appointmentsEmergency department presentationsNon-elective hospital admissionsAI stethoscope utilisation ratesCompletion of site setup for all practices in intervention groupData fidelity—ascertainment

The following interim outcomes will be considered significant and warranting intervention:

Mean AI-stethoscope utilisation rate of less than five recordings per month per practice in the intervention armHealthcare diagnostics utilisation differential affecting patient safetyIncomplete site setup in intervention group

In keeping with formative evaluations in implementation research^29^,^31^ and behavioural change frameworks,^43^ adaptive interventions will be considered prospectively to maximise the success of the implementation of AI stethoscope (given the established confidence for the technology ‘working’ on the basis of widely validated statistical accuracy). In addition, prespecified interventions will be available to the Steering Committee following the interim analysis.

Semistructured interviews of high- and low-use participantsProvision of repeat training in the use of the AI stethoscopeRedistribution of the AI stethoscope to new, prospectively enrolled GP practicesProvision of latest generation of the AI stethoscope hardware and software to intervention groupIntegration of the AI stethoscope system with the electronic health record system

To mitigate lead-time effects, interim analysis of the coprimary endpoints will not incur a stopping rule at 6 months. If at 6 months there is no statistically significant difference between treatment arms for the coprimary endpoints, then a further interim review will be performed at 12 months. If there remains no clinically significant difference in the coprimary endpoint at 12 months, the Trial Steering Group will have the option to stop the trial on the basis of futility.

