### Study design

TRICORDER is an open-label, two-arm cluster-randomised controlled trial. Taking a decentralised approach, primary care practices in the NHS North West London Integrated Care System (NWL ICS, 2.8 million residents, figure 2) and the Betsi Cadwaladr University Health Board (BCUHB, 670 000 residents) in North Wales, UK, will be enrolled for 18 months.

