### Control arm

Primary care practices in the control arm will continue with usual clinical care, with decision-making for consideration of HF, and initiation of the NICE diagnostic pathway based on clinical judgement alone.

Participating practices can withdraw at any time. If a primary care practice ceases face-to-face consultations during the study, they will be withdrawn from the study by the research team.

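### The Steering Committee is to stay blinded to study end, yet one interim report gives it outcomes by group alongside device-only data, and under that blind its safety trigger can be detected but not interpreted

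*Protocol article*

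**What the plan says.** All of this is in the protocol article, mostly under Interim analysis.

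- **Blinding.** The interim results "will be reviewed by the Trial Steering Committee, who will remain blinded to the treatment allocation of each group until the study end".
- **Content of the report.** The same report carries both coprimary comparisons, the first being "Difference in the incidence of coded HF between groups". It also carries diagnostics use, primary care appointments, emergency attendances, non-elective admissions, AI stethoscope utilisation, completion of set-up at intervention practices, and data ascertainment.
- **Triggers.** Three findings call for intervention: mean use below five recordings per practice per month in the intervention arm, a difference in diagnostics use that bears on patient safety, and incomplete set-up in the intervention group.
- **Remedies.** The section says that "prespecified interventions will be available to the Steering Committee following the interim analysis". The five listed are interviews with high and low users, repeat training, moving devices to newly enrolled practices, newer hardware and software for the intervention group, and integration with the health record.
- **Outcome-based decisions.** The section says that "interim analysis of the coprimary endpoints will not incur a stopping rule at 6 months". A 12-month review follows if the coprimary endpoints show no statistically significant difference at 6 months. "If there remains no clinically significant difference in the coprimary endpoint at 12 months", stopping for futility becomes an option.
- **Arms.** Study design states: "TRICORDER is an open-label, two-arm cluster-randomised controlled trial". Control arm states: "Primary care practices in the control arm will continue with usual clinical care".

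**The concern.** The section asks two things of one committee that do not fit together as written. It is not to know which group is which until the trial ends. It is also to receive data that exist in only one of the two groups, and to act on a safety difference whose meaning depends on which group has the device.

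There is a cost on either side. If device data and outcomes arrive in one table by group, the committee is in effect unblinded at 6 months, while the publication describes blinded oversight. The same committee holds remedies that strengthen the intervention, so a reader could not rule out that a change in the intervention was influenced by the emerging coprimary result. If the blind is enforced to study end, the committee may see a worrying gap in diagnostics use and be unable to say what kind of problem it is.

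**Working it through.** No formula applies, and the plan gives no figure to reproduce. The check takes each item in the Interim analysis section and asks what the committee must know to use it. There are two kinds of knowledge:

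- (a) that a given set of data comes from device practices;
- (b) which masked outcome column, A or B, is the device arm.

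Only (b) breaks a blind to the allocation of each group.

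| Item | Needs (a) | Needs (b) |
|---|---|---|
| Trigger: low device use | yes | no |
| Trigger: incomplete set-up | yes | no |
| Trigger: diagnostics difference, to detect a gap | no | no |
| Trigger: diagnostics difference, to read its direction and attribute it to the device | yes | **yes** |
| The five remedies | yes | no |
| 12-month futility: judging that no difference is present | no | no |
| 12-month review: which arm a difference favours | yes | **yes** |

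**Report content.** The section lists two coprimary and seven secondary items, nine in all. Two of the nine, utilisation and set-up, have no counterpart in the control arm, because control practices continue usual care and are given no device. Put in columns A and B beside the outcomes, either item shows which column is the device arm. The text neither says they are tabulated this way nor says they are kept apart.

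**Triggers.** Two of the three name the intervention arm or group, but both can be read from a stand-alone report on device practices. The third is a difference, taken here to be between groups, with no stated direction or size. Under masked labels the committee can see that A exceeds B. If A is the device arm, the device practices are generating more diagnostics; if B is, they are generating fewer. Those are opposite safety questions, and masked data cannot tell them apart. The blinding sentence runs to study end and states no earlier exception.

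**Remedies.** All can be ordered for device practices without knowing the outcome columns. The section does not expressly say that the choice must rest on utilisation and set-up alone.

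**The case against.** The strongest reply is that a blind to the allocation of each group can simply mean masked outcome labels, and such a blind is workable. Use and set-up are worded as intervention-arm items, which fits a separate implementation report. An article does not normally set out report layout or unblinding routes; the full protocol or a committee charter, not shown here, may do so. An open-label trial can also have a committee masked to aggregate outcomes.

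Most of this stands, and it limits the point in four ways.

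- A reader might infer that the blind cannot hold at all. The documents do not support that: the use and set-up triggers and all the remedies can operate without linking outcome labels to arms.
- A reader might infer that the committee will see unmasked coprimary results and adjust the intervention accordingly. The document does not say so, and none of the three triggers is a coprimary endpoint.
- A reader might say the safety trigger cannot be applied. A gap can be detected under masked labels; only its direction and attribution are lost.
- A reader might extend the problem to the 12-month futility decision. The decision described there turns on the absence of a difference, which can be judged blind.

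What the reply does not remove is the conflict between two rules that are both stated: a blind to study end, and a duty to act on a safety difference that cannot be interpreted under that blind. That is more than missing detail. A charter providing a split report and a safety exception would settle the practice, but the published sentence would still need the exception.

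**Conclusion.** The Interim analysis section is in tension with itself and should be reconciled. As written, nothing in the text protects the blind, because two of nine report items identify the device arm if shown by group beside the outcomes. If the blind is kept as stated, one of three triggers, the safety one, can be detected but not read as an excess or a deficit in the device arm.

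This is a matter of oversight and reporting. It does not show that blinding is impossible, and no power, type I error or sample-size figure changes. The conclusion rests on two readings: that the diagnostics difference is a comparison between groups, and that the words about study end allow no earlier unblinding. Confidence is high that the conflict is in the text. How the committee would work in practice cannot be known from this document.

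**What to change.** Reconcile the blinding statement with the triggers in the Interim analysis section:

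1. Put utilisation, set-up and data ascertainment in a separate implementation report, and show outcomes only under masked group labels. Check that practice counts in the first report do not match a group size in the second, since that would also give the labels away.
2. Replace the unqualified blind to study end with a stated exception: the committee, or a designated unblinded reviewer from among the existing roles, may see the arm labels when a diagnostics or other safety difference has to be judged.
3. State that the prespecified implementation remedies are chosen on utilisation and set-up metrics, and not on the coprimary results.

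If the sponsor will not do this, drop the claim that the committee is blinded.

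The cost is protocol wording and a slightly more complex report, with no new committee. The downside is possible partial unblinding if a safety difference arises. Three larger changes are separate or debatable design choices and are not needed here: removing the blind outright as the first choice, showing emergency and admission data by named arm (which could inform on the second coprimary endpoint, the ratio of hospital to community diagnoses), and making the 12-month review unconditional.

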### Sample size

Interrogation of the Discover dataset^37^ (UK Secure Data Environment for TRICORDER endpoint analysis) suggests an incidence rate of HF of 0.62/1000 patients per year. Combining NWL (n=350) and North Wales (n=>50), there are at least 400 potentially eligible study sites. We estimate that each GP practice will have at least 60 eligible patients per year who will receive a stethoscope examination as part of their routine clinical care. Estimating a conservative recruitment ratio of only 50%, we anticipate 200 GP practices being recruited. This provides an eligible study population of 6000 patients per study arm. A review of prior literature in the field indicates an intracluster correlation coefficient of 0.01.^38^

Utilising these estimates and assumptions, we would have over 80% power to detect a statistically and clinically significant mean difference if HF is diagnosed at a rate of 0.79/1000 patients in the intervention group, assuming a two-tailed test with a type I error of 0.05. This corresponds to a relative increase of 22%, which is deemed to be clinically meaningful (~17 to 22 HF diagnoses/GP practice).

The power calculation refers to overall HF, which includes all relevant ICD-10 and SNOMED-CT codes (used in UK primary care), rather than the codes relating to HFrEF specifically. There are three reasons for such an inclusive approach.

First, we aim to mitigate an artificially low incidence of HFrEF due to coding heterogeneity in primary care. Preliminary analysis of the Discover dataset revealed substantial heterogeneity in clinical coding of HF subtypes. This is well recognised in recent studies.^39^

Second, this approach captures the effect on clinician behaviour from participation in the study—it is feasible that more of all HF subtypes may be detected during the study period.

Finally, this approach enables rapid clinical and health economic endpoint analysis, avoiding the time and cost burden of manual data entry/data collection from chart arbitration, which would otherwise risk undermining the scalability of TRICORDER and set an impractical precedent for longer-term outcomes analyses.

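### The 12-month futility criterion is undefined and of the wrong kind; read as the design target, it would make about half of truly on-target trials eligible for the optional stop

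*Protocol article*

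**What the plan says.** All of the interim wording is in the protocol article, section Interim analysis. The first look is fixed in calendar time: "An interim analysis will be performed 6 months after the first site has been randomised". It carries no stopping rule, and the section gives lead-time effects as the reason. A second review is conditional: "If at 6 months there is no statistically significant difference between treatment arms for the coprimary endpoints", a further review follows at 12 months. The futility provision is then: "If there remains no clinically significant difference in the coprimary endpoint at 12 months, the Trial Steering Group will have the option to stop". The section gives no number for a clinically significant difference and does not restate the origin of the 12-month clock.

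The Study design section says that practices "will be enrolled for 18 months". The Sample size section is the only place that ties clinical significance to a figure. For the intervention arm it claims "over 80% power to detect a statistically and clinically significant mean difference if HF is diagnosed at a rate of 0.79/1000 patients", against a control figure from a dataset that "suggests an incidence rate of HF of 0.62/1000 patients per year". It adds: "This corresponds to a relative increase of 22%, which is deemed to be clinically meaningful". Box 1 lists two coprimary endpoints: incidence of coded heart failure, and the ratio of hospital-based to community-based diagnoses.

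**The concern.** A futility rule should ask whether the data so far leave a realistic chance of a positive final result. This one asks whether a worthwhile difference has already been seen. Those are different questions: an interim estimate from an effective trial is scattered around the true effect, and if the mark is the effect the trial was designed to find, the estimate falls short of it about as often as not.

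The wording adds three ambiguities. The word *remains* joins a statistical test at 6 months to a clinical one at 12 months as if they were the same. The plural endpoints become a singular one, so it is unclear whether one miss or two are needed, and which endpoint governs. And the 12-month review is held only after a non-significant 6-month result, so a chance early positive removes it, although the same paragraph worries about early timing.

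At stake is a steering group deciding, with interim results in hand, what its own criterion means, and possibly ending a trial of an intervention that works as planned.

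**Working it through.** **Inputs from the article.** Two-sided 5% test ("assuming a two-tailed test with a type I error of 0.05"); stated power over 80%; 0.62 versus 0.79 per 1000; 6000 patients per arm; intracluster correlation 0.01; 60 patients per practice per year; 18 months of enrolment.

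**The plan's own figure.** The article gives no operating characteristic for the futility rule, so the only figure to reproduce is the power. With 6000 per arm, a two-proportion test of 0.62 versus 0.79 per 1000 has 5.4% power without clustering. With design effect 1 + 59 × 0.01 = 1.59 it has 4.6%. The stated power is not reproduced, so 80% is used below as an assumption. The target also has two versions: 0.79/0.62 = 1.274, an increase of 27.4%, against the stated 22% (0.17/0.79 = 21.5%).

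**Assumed information fractions t at 12 months.** The article gives no recruitment pattern. If every practice is followed for 18 months:

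- all start together: t = 12/18 = 2/3 at 12 months, 6/18 = 1/3 at 6 months;
- even entry over 6 months: mean follow-up 9/18 = 1/2, and 3/18 = 1/6;
- even entry over 12 months: mean follow-up 6/18 = 1/3, and (1/2 × 3)/18 = 1/12.

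**Formula.** With drift θ = 1.960 + 0.842 = 2.80 (80% power at the target), the true effect at the target, and a cut-off of f times the target:

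P(estimate below cut-off) = Φ((f − 1) × 2.80 × √t)

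| Cut-off | t = 1/3 | t = 1/2 | t = 2/3 |
|---|---|---|---|
| Target (f = 1) | 0.50 | 0.50 | 0.50 |
| 22% when the truth is 27.4% (f = 0.80) | 0.37 | 0.35 | 0.33 |
| Half the target (f = 0.5) | 0.21 | 0.16 | 0.13 |
| Zero (f = 0) | 0.05 | 0.02 | 0.01 |

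The first row is Φ(0). It does not depend on t, sample size, clustering or the assumed power.

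**Allowing for the 6-month condition.** The review takes place only if the 6-month result is not significant. Taking the two z-values as bivariate normal with correlation √(t6/t), and the cut-off at the target, the joint probability is 0.43 for (t6, t) = (1/3, 2/3), 0.46 for (1/6, 1/2) and 0.48 for (1/12, 1/3).

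**If both endpoints must miss.** For independent endpoints, each with its true effect exactly at its cut-off: 0.5 × 0.5 = 0.25.

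**Power if the option is always used at the target cut-off**, ignoring the 6-month condition: P(z12 ≥ 2.80√t and z18 > 1.96) with correlation √t is 0.47, 0.48 and 0.49 at t = 1/3, 1/2 and 2/3.

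**A conditional-power rule for comparison**, at t = 2/3, stopping when conditional power under the design effect is below 20%:

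- cut-off z = (1.96 − 0.842 × √(1/3) − 2.80 × 1/3)/√(2/3) = 0.66;
- stops under the target effect: Φ(0.66 − 2.80 × 0.816) = 0.052;
- stops under no effect: Φ(0.66) = 0.746;
- power kept: 0.795, against 0.80 without a rule.

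**The case against.** The strongest reply is that the section gives the steering group an option. The rule is already non-binding, and a sensible group would look at more than the point estimate. That stands. A reader might infer that the rule *would stop* half of effective trials; the article does not support this. Half is the share that would become eligible, and the power loss applies only if the option is used every time.

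Second, the cut-off is inferred. The Interim analysis section sets none, and a numerical definition could sit in an analysis plan that is not shown. This also stands, and it is why the result is a range from about 1% to 50%. But the article does state the type of criterion, the absence of an observed difference, and a number placed elsewhere would not change that type.

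Third, a reader might blame timing from the first site for the 50%. It does not cause it: at the target cut-off the figure is the same at every information fraction. Late entry matters only for lower cut-offs. Only the 6-month look is explicitly tied to the first site; the same clock at 12 months is the natural reading but is not stated.

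Fourth, the 6-month condition lowers the risk to an effective trial. True, from 50% to 43–48%, but it does so by dropping the review after an early result that may be chance.

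**Conclusion.** The point holds in a limited form. The 12-month criterion is undefined (no cut-off, a change in the kind of significance, one endpoint named for two), and it does not measure futility. If it means the design target, the article's only anchor, 43–50% of trials with a truly on-target effect would be eligible for the optional stop. The 50% needs no assumption beyond an unbiased interim estimate and that reading of the cut-off. An effect that builds slowly would raise it, but the article gives no lag from which to say by how much.

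The other figures (13–21%, 1–5%, and a fall to 47–49% power) assume 80% final power, which the Sample size inputs do not deliver, and information fractions of 1/3 to 2/3. The 25% assumes independent endpoints, each exactly at its cut-off. One sentence therefore supports error risks from about 1% to 50%, and being non-binding does not cure that. It should be corrected before the 12-month review.

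**What to change.** Keep the rule non-binding and reword it as follows.

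- **Criterion.** Base it on low conditional power, for example below 20%, under the design effect, after the 22% versus 27% conflict has been settled.
- **Endpoints.** Allow a futility stop only when the criterion holds for both coprimary endpoints, or state which one governs. The Sample size section gives a target for heart failure incidence only, so a design effect for the ratio has to be stated too.
- **Timing.** Tie the review to accrued follow-up, for example two-thirds of planned practice-months.
- **Condition.** Hold the review whatever the 6-month result.

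The cost is protocol wording, a short calculation at the review, and a review that may fall later in calendar time. For one endpoint with 80% power at two-thirds information, the power cost is about 0.5 percentage points (80% to 79.5%). Requiring both endpoints costs less power but stops fewer ineffective trials: under independence, with both endpoints null and the same cut-off, 0.746 × 0.746 = 56% instead of 75%.
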